| Study Drug Strength and Mode of Administration | 
Drug strength: The drug product strength is 2 mg/vial, and the placebo strength matches the drug product;
 
Mode of administration: subcutaneous injection, once weekly,
 
 
• Cohort 1: 1.0 mg for 4 weeks + 2.0 mg for 4 weeks + 3.0 mg for 4 weeks;
 
• Cohort 2: 1.5 mg for 4 weeks + 3.0 mg for 4 weeks + 4.5 mg for 4 weeks;
 
• Cohort 3: 2.0 mg for 4 weeks + 4.0 mg for 4 weeks + 6.0 mg for 4 weeks;
 
• Cohort 4: 2.5 mg for 4 weeks + 5.0 mg for 4 weeks + 7.5 mg for 4 weeks + 10.0 mg for 4 weeks;
 
• Cohort 5: 3.0 mg for 4 weeks + 6.0 mg for 4 weeks + 9.0 mg for 4 weeks.
 
                                                                                                                                                                                                                                                                                                                                                                                                                                                                                                                                                                                                                                                                                                                                                                                                                                   |

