| Blood sampling time window        | –         | ± 10 min | ± 20 min | ± 1 h | –         | –         | ± 1 h | ± 2 h | –   | ± 10 min | ± 20 min | ± 1 h | –         | –         | ± 1 h | ± 2 h | ± 12 h |
| Pre-dose                          | ✓         |          |          |       | ✓         | ✓         |       |       | ✓   |          |          |       | ✓         |           |       |       |        |
| Post-dose                         |           | ✓        | ✓        | ✓     |           |           | ✓     | ✓     |     | ✓        | ✓        | ✓     |           |           | ✓     | ✓     | ✓      |
| Vital Signs                       | ●         | ●        | ●        | ●     | ●         | ●         | ●     | ●     | ●   | ●        | ●        | ●     | ●         | ●         | ●     | ●     | ●      |
| PK sampling                       | ●         | ●        | ●        | ●     | ●         | ●         | ●     | ●     | ●   | ●        | ●        | ●     | ●         | ●         | ●     | ●     | ●      |
| Fasting plasma glucose            | ●         |          |          |       |           | ●         |       | ●     | ●   |          |          |       |           |           |       |       |        |
| Fasting insulin/fasting C-peptide | ●         |          |          |       |           | ●         |       | ●     | ●   |          |          |       |           |           |       |       |        |
| Fasting glucagon                  | ●         |          |          |       |           | ●         |       | ●     | ●   |          |          |       |           |           |       |       |        |
| Endogenous GLP-1                  | ●         |          |          |       |           | ●         |       | ●     | ●   |          |          |       |           |           |       |       |        |
| Endogenous OXM                    | ●         |          |          |       |           | ●         |       | ●     | ●   |          |          |       |           |           |       |       |        |

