**Notes:**

**1. PK Sampling Points**

Sampling points in Week 1 (intensive PK): within 1 h before dosing, 4 h ± 10 min, 8 h ± 20 min, 12 h ± 30 min, 24 h ± 1 h (Day 2), 48 h ± 2 h (Day 3), 72 h ± 3 h (Day 4), 96 h ± 4 h (Day 5), 120 h ± 5 h (Day 6) after dosing on D1. Sampling in Week 2: within 1h before administration on D8. Sampling in Week 4: within

1h before and  $24\text{h} \pm 1\text{h}$  after administration on D22. Sampling in Week 5: within 1 h before administration and  $4\text{h} \pm 10\text{ min}$ ,  $8\text{h} \pm 20\text{ min}$  and  $24\text{h} \pm 1\text{h}$  after administration on D29. Sampling at Week 6: within 1h before dosing at D36. Sampling in Week 8: within 1h before and  $24\text{h} \pm 1\text{h}$  after D50 administration. Sampling in Week 9: within 1 h before administration and  $4\text{h} \pm 10\text{ min}$ ,  $8\text{h} \pm 20\text{ min}$  and  $24\text{h} \pm 1\text{h}$  after administration on D57. Sampling at Week 10: within 1h before D64 administration. Sampling at Week 12: within 1h before administration and  $24\text{h} \pm 1\text{h}$  and  $48\text{h} \pm 2\text{h}$  after administration on D78. Sampling in Week 13: within 1 h before administration and  $4\text{h} \pm 10\text{ min}$ ,  $8\text{h} \pm 20\text{ min}$  and  $24\text{h} \pm 1\text{h}$  after administration on D85 (D86). Sampling at Week 14: within 1h before administration at D92. Sampling at Week 16: within 1 h before D106 administration,  $24\text{h} \pm 1\text{h}$  and  $48 \pm 2\text{h}$  after D106 administration, and  $168\text{h} \pm 12\text{h}$  after D106 administration (Day 113). If a subject fails to complete the study and prematurely withdraws from the study, PK samples will be collected at the Early Termination Visit. 3mL of whole blood will be collected at each blood collection point. Refer to the central laboratory manual for detailed operation procedures.

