## 2. PD (fasting insulin/fasting C-peptide/fasting plasma glucose/fasting glucagon/OXM/GLP-1) sampling points

Sampling points in Week 1: within 1h before administration (Day 1) and  $48\text{h} \pm 2\text{h}$  after administration (Day 3) on D1. Sampling in Week 2: within 1h before administration on D8. Sampling in Week 5: within 1h before administration on D29. Sampling at Week 9: within 1h before dosing on D57. Sampling at Week 12: within 1 h before dosing on D78 and  $48\text{h} \pm 2\text{h}$  after dosing on D78 (Day 80). Sampling at Week 13: within 1h before D85 administration. If a subject fails to complete the study and prematurely withdraws from the study, a PD sample will be collected at the Early Termination Visit. All PD sampling was performed under fasted conditions. A total of 9 mL of whole blood will be collected at each blood collection point. Detailed procedures will be described in the central laboratory manual.

6Table 6. Trial Procedures and Schedule of Assessments (Cohort 5)

| Study Phases and Procedures                     | Screening Period 1 | Double-Blind Treatment Period |                |                |                |                |                |                |                |                 |                 |                 |                 |                 |                 |                 |                 |                 |                 |                 |                 | Safety Follow-up |                 | Early Withdrawal |
|-------------------------------------------------|-------------------------------|-------------------------------|----------------|----------------|----------------|----------------|----------------|----------------|----------------|-----------------|-----------------|-----------------|-----------------|-----------------|-----------------|-----------------|-----------------|-----------------|-----------------|-----------------|-----------------|------------------|-----------------|------------------|

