### **2.2.2 Secondary Endpoints**

- To assess the pharmacokinetic parameters of IBI362 in overweight or obese subjects, including but not limited to:  $T_{max}$ ,  $C_{max}$ , Area Under Curve (AUC), volume of distribution ( $V_d$ ), half-life ( $T_{1/2}$ ), clearance (CL), accumulation coefficient (AR);
- To evaluate the pharmacodynamic parameters of fasting plasma glucose, fasting glucagon, fasting insulin, fasting C-peptide, endogenous oxyntomodulin (OXM) and glucagon-like peptide 1 (GLP-1) before and after multiple doses of IBI362;
- Changes from baseline in fasting body weight, waist-to-hip ratio, BMI, blood pressure, pulse rate, blood lipids and HbA1c at steady state in each dose period during dose escalation;
- Occurrence of anti-drug antibody (ADA) and neutralizing antibody (NAb) against IBI362 in serum before and after administration;
- Pancreatic  $\beta$ -cell function and insulin resistance (HOMA model) were evaluated.
- To assess the effect of IBI362 on serum uric acid and alanine aminotransferase in overweight or obese subjects.

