## **Cohort 4**

The starting dose of the subjects is 2.5 mg, once a week, after continuous administration for 4 weeks; If the subject is well tolerated #, the dose will be up-titrated to 5.0 mg once a week for consecutive 4 weeks; Observe the tolerance of the subjects again. If the tolerance is good #, the dose will be increased to 7.5 mg once a week for consecutive 4 weeks; Observe the tolerability of the subjects again. If the tolerability is good #, the dose will be increased to 10.0 mg once a week for consecutive 4 weeks (the dose will be increased by 2.5 mg every 4 weeks to the target dose).

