#### **6.3.3 PK/PD variables**

- Pharmacokinetic parameters, including but not limited to Tmax, Cmax, product under the concentration-time curve (AUC), volume of distribution (Vd), half-life (T1/2), clearance (CL) and accumulation coefficient (AR);
- Pharmacodynamic variables, including fasting plasma glucose, fasting glucagon, fasting insulin, fasting C-peptide, endogenous OXM, GLP-1.

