#### **8.4. 5 Analysis of Pharmacokinetic and Pharmacodynamic Parameters**

Each PK parameter, including but not limited to Tmax, Cmax, product under the concentration-time curve (AUC), volume of distribution (Vd), half-life (T1/2), clearance (CL) and accumulation coefficient (AR), will be summarized separately for each dose group.

Pharmacodynamic parameters, including fasting plasma glucose, fasting glucagon, fasting insulin, fasting C-peptide, endogenous OXM, and GLP-1, were summarized by group at baseline and at each time point after dosing, and changes from baseline at each time point were summarized.

The changes from baseline in fasting body weight, waist-to-hip ratio, BMI, blood pressure, pulse rate and blood lipids before administration and at 4 weeks (D29), 8 weeks (D57), 12 weeks (D85) and 16 weeks (D113) after administration were summarized and analyzed by groups. The change from baseline in HbA1c at pre-dose and at 12 and 16 weeks post-dose (D113) was analyzed in a pooled manner.

Changes from baseline in islet function (HOMA model) at each time point after treatment were summarized by group.

Changes from baseline in serum uric acid and alanine aminotransferase levels at each

time point after treatment were summarized by group.

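### Cohort 4 has no scheduled six-analyte pharmacodynamic sample, and so no HOMA estimate, after any 10 mg dose

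*Protocol*

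**What the plan says.** The dosing summary gives the last two steps of Cohort 4 as "7.5 mg for 4 weeks + 10.0 mg for 4 weeks", and section 3.2.1 says that after the 7.5 mg step "the dose will be increased to 10.0 mg once a week for consecutive 4 weeks". Table 4 places the 16 weekly injections on Days 1 to 106, so the 10 mg doses fall on Days 85, 92, 99 and 106.

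The PD note under Tables 5-1 and 5-2 ends its scheduled draws with "Sampling at Week 13: within 1h before D85 administration". The rows of Table 5-2 for glucose, "Fasting insulin/fasting C-peptide", glucagon, GLP-1 and OXM are marked on Day 57 pre-dose, Day 78 pre-dose, Day 80 and Day 85 pre-dose, and nowhere later. The PK note goes on: "Sampling at Week 16: within 1 h before D106 administration", then 24, 48 and 168 hours after that dose.

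Section 6.3.3 defines the panel: "Pharmacodynamic variables, including fasting plasma glucose, fasting glucagon, fasting insulin, fasting C-peptide, endogenous OXM, GLP-1". Section 2.2.2 lists the panel as a secondary endpoint and adds that beta-cell function and "insulin resistance (HOMA model) were evaluated". Section 8.4.5 says the PD parameters "were summarized by group at baseline and at each time point after dosing", and plans a by-group summary of HOMA at each time point after treatment.

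Table 4 has a single combined PK/PD row, marked on Days 86, 92, 106, 107, 108 and 113. Its note 17 refers the reader to Tables 5-1 and 5-2, which make those visits PK only.

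**The concern.** PK/PD is the only secondary objective (section 2.1.2), and Cohort 4 contains the highest dose in the trial. If the panel stops before that dose starts, the trial cannot describe insulin, C-peptide, glucagon, OXM, GLP-1 or HOMA at 10 mg, and cannot set PD responses beside the PK collected in the same weeks. The analysis cannot repair this, because blood that was not drawn cannot be recovered. The combined row in Table 4 adds a practical risk: a site reading only that table could believe PD blood is due through Day 113, while a site following Table 5-2 would draw none.

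**Working it through.** No sample size, power or error rate is involved. The check is a count of scheduled draws by dose level.

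**Rule.** Each draw is assigned to the most recent injection before it, so a pre-dose draw belongs to the preceding dose.

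**Cohort 4 PD draws** (Tables 5-1 and 5-2 and the PD note):

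| Dose in effect | Injection days | PD draws | Count |
|---|---|---|---|
| None (baseline) | – | D1 pre-dose | 1 |
| 2.5 mg | D1, 8, 15, 22 | D3, D8 pre-dose, D29 pre-dose | 3 |
| 5.0 mg | D29, 36, 43, 50 | D57 pre-dose | 1 |
| 7.5 mg | D57, 64, 71, 78 | D78 pre-dose, D80, D85 pre-dose | 3 |
| 10.0 mg | D85, 92, 99, 106 | none | 0 |

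Total: 1 + 3 + 1 + 3 + 0 = 8.

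**PK draws in the 10 mg step** (Table 5-2 and the PK note): D85 at 4 h and 8 h, D86, D92, D106 pre-dose, D107, D108, D113. That is 8.

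**Top-dose PD draws in the other cohorts** (Tables 3-2 and 7-2). Cohorts 1, 2, 3 and 5 start their top dose (3.0, 4.5, 6.0 and 9.0 mg) on D57 and take the last dose on D78. D78 pre-dose, D80 and D85 (168 h after the last dose) all fall on the top dose: 3 draws each, against 0 in Cohort 4.

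**HOMA.** It needs fasting glucose paired with fasting insulin or C-peptide. Routine fasting glucose is scheduled on D113, but no insulin or C-peptide is scheduled after D85 pre-dose. Scheduled HOMA time points at 10 mg: 0.

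**What is still measured on D113.** Table 4 marks weight, waist, hip, vital signs and the routine laboratory panel, which includes lipids, uric acid, ALT and fasting glucose. HbA1c goes to the central laboratory. Section 8.4.5 plans a D113 summary of weight, waist-to-hip ratio, BMI, blood pressure, pulse rate and lipids.

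**Blood volume.** From the volumes in the notes, Cohort 4 currently has PK 36 × 3 = 108 mL, PD 8 × 9 = 72 mL, immunogenicity 6 × 5 = 30 mL and central HbA1c 3 × 2 = 6 mL: 108 + 72 + 30 + 6 = 216 mL. This is a subtotal; routine safety blood is not in it. One more PD draw gives 216 + 9 = 225 mL, and three give 216 + 27 = 243 mL.

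**The case against.** The strongest reply is that no stated commitment is broken. The PD endpoint asks for values before and after multiple doses, and Day 85 comes after 12 of them. The requirement to report in each dose period belongs to a separate item covering weight, blood pressure, lipids and HbA1c. Each time point in section 8.4.5 can be read as each scheduled time point, and the 5.0 mg step has only one PD draw, so equal coverage was never promised. The stated reason for going higher (section 3.1.1) is weight loss activity, and weight is measured throughout the 10 mg step. The existing days also give a clean 12-week comparison across all five cohorts, whereas Day 113 in Cohort 4 against Day 85 elsewhere mixes dose with duration.

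Much of this stands. The gap limits what the trial can show about a secondary endpoint; it does not contradict that endpoint's wording. The caution about dose and duration is correct. But none of it supplies the five hormone measures or HOMA at 10 mg, and the protocol gives no reason for leaving them out.

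A reader might also infer more than the documents support:

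- That only glucose and HbA1c exist at 10 mg. Most other response measures are scheduled on Day 113.
- That no subject can have a 10 mg PD value. A subject who withdraws during that step gives one at the early termination visit.
- That 7.5 mg results will be reported as 10 mg results. No last-value PD summary is planned, and the last-observation rule in section 8.4.2 is given for efficacy endpoints and not stated to cover the PD panel.
- That the 12-week list was simply copied. The eight days are the same, but the Day 85 wording was adapted for Cohort 4, so the cause is not known.

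**Conclusion.** The point holds as a gap in the sampling schedule. Cohort 4 has 0 scheduled six-analyte PD draws, and 0 HOMA time points, after any of its four 10 mg doses, against 8 PK draws in the same step and 3 top-dose PD draws in every other cohort. Table 5-2 and its note agree, so the gap does not come from a misread table. Table 4 obscures it by marking a combined PK/PD row at visits that are PK only.

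It should be fixed, but it does not threaten the trial. It concerns one descriptive secondary panel in one cohort of 12 (8 active, 4 placebo); the primary safety endpoint is untouched and no formal test depends on it. The conclusion rests on two assumptions: pre-dose samples reflect the preceding dose, and note 17 of Table 4 gives Tables 5-1 and 5-2 precedence.

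**What to change.** Add the six-analyte panel to Table 5-2 and the Cohort 4 PD note on Day 113, 168 hours after the last 10 mg dose. Preferably add Day 106 pre-dose and Day 108 as well, to mirror Days 78, 80 and 85 in the other cohorts. Use Day 113 for the Cohort 4 end-of-treatment PD and HOMA summary, keep Day 85 for the same-week comparison across cohorts, and state that Day 113 against Day 85 elsewhere mixes dose with duration.

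The cost is wording in the protocol and laboratory manual, plus 9 mL per subject for one draw (12 samples) or 27 mL for three (36 samples). All of these visits already take PK blood. No dose, visit or clinical rule changes.

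If the omission is intended, or the visits have passed without these samples, say that PD and HOMA in Cohort 4 end at 7.5 mg, label the Day 85 values accordingly, and split the combined row in Table 4 into PK and PD.

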**Notes:**

1. If the examination at screening is more than 5 days away from the day of administration, it should be confirmed again within 5 days before administration, including vital signs, physical examination, hematology, blood biochemistry, lipid profile, coagulation function, urinalysis, myocardial enzymes, serum amylase and lipase, thyroid function, serum calcitonin, ECG and pregnancy test.
2. Window for vital signs: to be completed within 1 hour prior to dosing (except for non-dosing visits).
3. Physical examination: in the physical examination of skin and mucosa after administration, attention should be paid to the observation of abnormalities at the injection site. In addition to the examination time points listed in the table, the local skin and mucous membrane at the injection site should be observed for abnormalities immediately ( $\pm 2$  min), 20 min ( $\pm 5$  min), 40 min ( $\pm 5$  min) and 60 min ( $\pm 5$  min) after administration, including but not limited to skin erythema/redness, swelling, pain/tenderness, congestion/hemorrhage, etc.
4. Body weight: The subjects were required to take off their coat after urination and fasting at each measurement. The same subject used the same scale each time and avoided strenuous exercise before measurement.
5. Waist circumference: (1) standing position, relaxed shoulders and abdomen, smooth breathing, feet 25-30cm apart; (2) The horizontal position of measurement: the midpoint of the line between the anterior superior iliac spine and the inferior margin of the 12th costal line on the midaxillary line; (3) Use a tape ruler around the abdomen in the above-mentioned horizontal position, with the tape ruler closely adhering to the skin, but not strangling the skin; (4) The measurement should not be made consciously with the abdomen closed or lifted, and the measurement should be taken at the calm end of expiration, with the waist circumference in cm to the nearest mm (e.g., 89.3 cm).

6. Hip circumference: (1) The subject stands naturally, with shoulders relaxed, arms naturally drooping and moderately open, legs together, legs evenly loaded, hips relaxed, and eyes ahead; (2) Horizontal positions measured: symphysis pubis anteriorly and greater trochanter of femur posteriorly; (3) Generally equivalent to the most protruding part of the buttock; (4) Wrap the buttocks horizontally with a tape ruler and record the values.
7. [6.2.1](#)Laboratory tests include: (refer to Section 6.2. 1)
  - 1) Hematology: white blood cell count (WBC), red blood cell count (RBC), platelets (PLT), hemoglobin (HGB), hematocrit (HCT), differential white blood cell count (neutrophils (ANC), basophils (BASO), eosinophils (EOS), monocytes (MONO) and lymphocytes (LYM));
  - 2) Blood biochemistry: aspartate aminotransferase (AST), alanine aminotransferase (ALT), total bilirubin (TBIL), direct bilirubin (DBIL), albumin (ALB), total protein (TP), glutamyl transpeptidase (GGT), alkaline phosphatase (ALP), lactate dehydrogenase (LDH), serum potassium, serum sodium, serum calcium, serum chloride, uric acid (UA), urea (Urea), creatinine (Cr), fasting serum glucose (FBG);
  - 3) Blood lipids: total cholesterol (TC), triglyceride (TG), high-density lipoprotein cholesterol (HDL-C), low-density lipoprotein cholesterol (LDL-C);
  - 4) Coagulation function: prothrombin time (PT), activated partial thromboplastin time (APTT), international normalized ratio (INR);
  - 5) Urinalysis: urine pH, urine protein (URPO), urine glucose (UGLU), urine red blood cells (URBC), urine white blood cells (UWBC);
  - 6) Myocardial enzyme spectrum: creatine kinase (CK), creatine kinase isoenzyme (CK-MB);
  - 7) Blood amylase, blood lipase.
8. Urine drug screen should include: morphine, dimethylenedioxyamphetamine, ketamine, tetrahydrocannabinolic acid, methamphetamine.

9. 212-lead electrocardiogram (ECG) parameters include: RR interval, PR interval, heart rate (HR), QT interval, QTcF (refer to Appendix 3 for calculation formula). Time points of examination: 1W: screening period, within 1h before the first administration, 12h after administration, 24h after administration (D2), 48h after administration (D3), 72h after administration (D4); 2W: within 1h before the second administration; 3W: within 1h before the third administration; 4W: within 1h before the 4th administration and 24h after administration (D23); 5W: within 1h before the 5th administration and 24h after administration (D30); 6W: within 1h before the 6th administration; 7W: within 1h before the 7th administration; 8W: within 1h before and 24h after the 8th administration (D51); 9W: within 1h before the 9th administration and 24h after administration (D58); 10W: within 1h before the 10th administration; 11W: within 1h before the 11th administration; 12W: within 1h before the 12th administration, 24h after administration (D79), 48h after administration (D80) and 72h after administration (D81, time window  $\pm 2$  h); 168h after the last dose (D85), safety follow-up (D106, D134). If the subject has abnormal ECG, the investigator can perform additional ECG according to the actual situation. The window period for ECG examination at each visit refers to the window period for PK sampling at the same time point.
10. Serological detection of infectious diseases: including human immunodeficiency virus (HIV) antibody, hepatitis B virus (HBV), hepatitis C (HCV) antibody and syphilis antibody.
11. [5.4.2](#) Blood pregnancy test for women of childbearing potential (refer to Section 5.4. 2 for the definition of childbearing potential)
12. Thyroid function measures include: thyroid stimulating hormone (TSH), free triiodothyronine (FT3), and free thyroxine (FT4).
13. Glycosylated hemoglobin test in central laboratory: blood collection points are at V2 visit (D1) and V20 visit (D85) and unscheduled. 2 mL of whole blood will be collected at each blood collection point. Refer to the central laboratory manual for detailed operation procedures.

14. 4For subjects with fasting blood glucose of 6.1-7.0 mmol/L at screening, venous blood glucose 2 hours after OGTT glucose load should be collected for confirmation. Refer to Appendix 5 for OGTT method.
15. Dual-energy X-ray (DEXA) and abdominal MRI are recommended to be performed at sites where conditions permit. DEXA method determination: The subject lies on the examination table, uses the DEXA standard mode, the scanning frame moves from the head side to the foot side, and scans. The scanning conditions were voltage ( $76 \pm 3$ ) KV and current 0.15 mA, tube voltage of two X-rays was 38 V and 70 KV, respectively, the scanning particle range was 197 cmx60 ca, the width was fixed at 60 cm, the scanning time was about 5 min, and the radiation absorber was 0.002 mGy. At the end of the measurement, DEXA device automatically recorded the fat weight of the whole body, waist and buttocks and other parameters, and calculated the waist-buttock fat ratio: waist fat weight (g)/buttock fat weight (g). PLODIGY dual-energy X-ray absorptiometry (Lunar, GE Company, USA) was recommended as the equipment used.
16. Immunogenicity sampling points: Week 1 (within 1h before dosing on Day1), Week 5 (within 1h before dosing on Day29), Week 9 (within 1h before dosing on Day57), Week 13 ( $168 \text{ h} \pm 12 \text{ h}$  after dosing on Day78) and Follow-up Visit on Week 20. If a subject withdraws early, whenever possible, 1 immunogenicity sample will be collected at the early withdrawal visit. 5 mL of whole blood will be collected at each blood collection point. Detailed procedures will be described in the central laboratory manual.
17. **77**Refer to Table 7-1 and Table 7-2 for PK/PD sampling points.
18. In this study, fasting blood collection was required to be fasted for at least 8 hours, and the drug was administered after fasting blood collection and then fed.
19. Eligible subjects should be admitted to the ward before the first dose. During hospitalization, they should have a unified diet and be prohibited from strenuous exercise, coffee and strong tea. They should be hospitalized for at least 3 consecutive days, i.e., complete PK/PD and ECG and other relevant examinations required on D3. They can temporarily leave the hospital after assessment by the investigator. However, subsequent visits should be conducted according to the time specified in the protocol. If conditions permit, it is recommended to be hospitalized before and after the 4th dose, before and after the 5th dose, before and after the 8th dose, before and after the 9th dose, and before and after the 12th dose to complete the examinations required by the visit.
20. ● Central laboratory testing.

7Table 7-1. PK/PD Sampling Schedule (1-5w)--Cohort 5

| Weeks of Dosing                   | 1W        |          |          |          |       |       |       |       |       | 2W        | 4W        |       | 5W        |          |          |       |
|-----------------------------------|-----------|----------|----------|----------|-------|-------|-------|-------|-------|-----------|-----------|-------|-----------|----------|----------|-------|
| Dosing Days                       | D1        |          |          |          | D2    | D3    | D4    | D5    | D6    | D8        | D22       | D23   | D29       |          |          | D30   |
| Blood sampling time               | Within-1h | 4h       | 8h       | 12h      | 24h   | 48h   | 72h   | 96 h  | 120 h | Within-1h | Within-1h | 24h   | Within-1h | 4h       | 8h       | 24h   |
| Blood sampling time window        | –         | ± 10 min | ± 20 min | ± 30 min | ± 1 h | ± 2 h | ± 3 h | ± 4 h | ± 5 h | –         | -         | ± 1 h | –         | ± 10 min | ± 20 min | ± 1 h |
| Pre-dose                          | ✓         |          |          |          |       |       |       |       |       | ✓         | ✓         |       | ✓         |          |          |       |
| Post-dose                         |           | ✓        | ✓        | ✓        | ✓     | ✓     | ✓     | ✓     | ✓     |           |           | ✓     |           | ✓        | ✓        | ✓     |
| Vital Signs                       | ●         | ●        | ●        | ●        | ●     | ●     | ●     | ●     | ●     | ●         | ●         | ●     | ●         | ●        | ●        | ●     |
| PK sampling                       | ●         | ●        | ●        | ●        | ●     | ●     | ●     | ●     | ●     | ●         | ●         | ●     | ●         | ●        | ●        | ●     |
| Fasting plasma glucose            | ●         |          |          |          |       | ●     |       |       |       | ●         |           |       | ●         |          |          |       |
| Fasting insulin/fasting C-peptide | ●         |          |          |          |       | ●     |       |       |       | ●         |           |       | ●         |          |          |       |
| Fasting glucagon                  | ●         |          |          |          |       | ●     |       |       |       | ●         |           |       | ●         |          |          |       |
| Endogenous GLP-1                  | ●         |          |          |          |       | ●     |       |       |       | ●         |           |       | ●         |          |          |       |
| Endogenous OXM                    | ●         |          |          |          |       | ●     |       |       |       | ●         |           |       | ●         |          |          |       |

Table 7-2. PK/PD Sampling Schedule (6-13w)--Cohort 5

| Weeks of Dosing                   | 6W        | 8W        |       | 9W        |          |          |       | 10W       | 12W       |       |       | 13W                  |
|-----------------------------------|-----------|-----------|-------|-----------|----------|----------|-------|-----------|-----------|-------|-------|----------------------|
| Dosing Days                       | D36       | D50       | D51   | D57       |          |          | D58   | D64       | D78       | D79   | D80   | D85                  |
| Blood sampling time               | Within-1h | Within-1h | 24h   | Within-1h | 4h       | 8h       | 24h   | Within-1h | Within-1h | 24h   | 48h   | 168h after last dose |
| Blood sampling time window        | –         |           | ± 1 h | –         | ± 10 min | ± 20 min | ± 1 h | –         | –         | ± 1 h | ± 2 h | ± 12 h               |
| Pre-dose                          | ✓         | ✓         |       | ✓         |          |          |       | ✓         | ✓         |       |       |                      |
| Post-dose                         |           |           | ✓     |           | ✓        | ✓        | ✓     |           |           | ✓     | ✓     | ✓                    |
| Vital Signs                       | ●         | ●         | ●     | ●         | ●        | ●        | ●     | ●         | ●         | ●     | ●     | ●                    |
| PK sampling                       | ●         | ●         | ●     | ●         | ●        | ●        | ●     | ●         | ●         | ●     | ●     | ●                    |
| Fasting plasma glucose            |           |           |       | ●         |          |          |       |           | ●         |       | ●     | ●                    |
| Fasting insulin/fasting C-peptide |           |           |       | ●         |          |          |       |           | ●         |       | ●     | ●                    |
| Fasting glucagon                  |           |           |       | ●         |          |          |       |           | ●         |       | ●     | ●                    |
| Endogenous GLP-1                  |           |           |       | ●         |          |          |       |           | ●         |       | ●     | ●                    |
| Endogenous OXM                    |           |           |       | ●         |          |          |       |           | ●         |       | ●     | ●                    |

